**19. SMS DEVELOPMENT AND DISPERSAL**

The messages will be developed by a team involving the principal investigator, supervisor, general physicians, endocrinologists and a nurse. Also, health education materials from the National Diabetes Education Programme will be used. Once the messages have been developed, they will be sent to several individuals including those with no formal education in order to ascertain its simplicity. The questions will be developed based on the principles of the behavioural change theory (Leventhal & Cameron, 1987). SMS will be dispersed to all participants in the intervention arm on a daily basis over the period of study at an agreed time of the day.

**20**. **ETHICAL CONSIDERATION**

The ethical approval for this study will be sought for from the University of Fort Hare Research Ethics Committee. Approval will also be sought from the Eastern Cape and the sub-districts Departments of health. Lastly, approval will be sought from the clinic managers. Also, verbal and written informed consent will be obtained from the participants before the commencement of the study.

**21. DATA ANALYSIS**

All treatment evaluations will be performed on the principle of intention-to treat (ITT), using the observed data collected from all randomised participants. Comparison of the baseline and the subsequent readings of the HbA1c will be determined. Primary outcome will be analysed with the chi-square. Descriptive statistics will be used to summarise the demographic and baseline characteristics. Continuous variables will be summarised as numbers of observed values, means, standard deviation, median, minimum and maximum. Categorical variables will be described as frequency and percentage. Linear regression model will be used to test the effect of intervention on the primary outcome between the two groups. All statistical tests will be two-sided at 5% significance level. The Statistical Package for Social Sciences (SPSS) version 22 will be used for all statistical analysis.

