**14. SAMPLE SIZE**

Standard care for diabetes using metformin has been reported to reduce HbA1c by 1% and the intervention adds an extra 0.5% (Amod et al., 2012; Pal et al., 2013:22). Assuming a standard deviation of 1 and an alpha error level of 5%, the two-tailed calculation gives a power of over 90% with only 90 participants in each of the control and intervention group. If 20% loss of participants to follow-up is considered (Islam et al., 2014), a total of 108 participants is required in each group.

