**15. RANDOMISATION AND BLINDING**

In order to avoid sharing of messages among diabetic patients, different districts will be used for the control and the intervention. The guideline for the management of diabetes is similar across all the primary health centres in South Africa (Amod et al., 2012), thus, all the primary health care centres are eligible. Of all the eight municipalities/districts, two were conveniently selected. In each selected district, the diabetes clinics were assessed for available facilities such as human resources, HbA1c testing, available diabetes support programmes. The information were obtained from the various facilities or unit heads as deemed appropriate. The obtained information were scored and used to stratify the diabetes clinics into two levels; average and low resourced clinics. All the clinics were assigned an identification number which were hidden from the study statistician. One average-resourced and two low-resourced clinics were selected from the two selected districts, summing up to 6 clinics; 4 low resourced and 2 high resourced clinics. From the clinics selected, demographic and other basic information were obtained to screen for eligibility. From the sample size calculation, 108 participants are required in both arms of the study, therefore, 36 participants are required from each of the six selected clinics. After the collection of the baseline data, randomisation will take place, where individuals are randomly assigned to either the intervention or the control arm using a simple randomisation technique with a 1:1 allocation ratio using the assigned ID numbers. The study statistician will randomly select 36 participants from the list of eligible participants from each clinic, adjusting for age and mean duration of diabetes. Participants in the intervention arm will then be contacted to ascertain their preferences in terms of the preferred language of communication; either the locally spoken Xhosa language or English, preferred time of receiving SMSs, name and contact of next of kin or the available support person.

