**18. SECONDARY OUTCOME MEASURES**

The secondary outcome measures will be assessed at three and six months namely;

- Knowledge on diabetes which will be obtained with the validated Michigan Diabetes Knowledge Test Questionnaire-2 (Fitzgerard et al., 2016).
- Medication adherence, using a pre-validated self-developed medication adherence questionnaire.
- Clinic attendance, using clinic registers.
- Quality of life, using the EQ-5D self-perceived quality of life questionnaire (EURO-QOL Group, 2009).
- Barriers to SMS intervention and the healthcare providers’ perception about SMS use using a self-designed questionnaire.
- Clinical (hypertension, overweight/obesity) and behavioural outcomes (Smoking, alcohol use, and physical activity) will be measured using the WHO modified STEPwise approach.
- Factors affecting adherence to diabetes therapy using a self-designed questionnaire

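### The primary analysis is called intention-to-treat but fixed on observed data, so the planned 20% loss makes it a complete-case comparison that may be biased, in either direction, if loss differs between arms

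*Protocol*

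**What the plan says.** Section 21 (Data analysis) applies intention-to-treat to all treatment evaluations, "using the observed data collected from all randomised participants". For the primary outcome it names a chi-square test and a linear regression of the intervention effect. No covariates are given for the regression.

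Section 17.1 defines the primary outcome as the change in random blood glucose from baseline to six months. Section 16 schedules data collection at those two times only. Section 18 adds a three-month assessment for the secondary outcomes, and glucose is not among them. The timeline in section 24 lists a three-month collection without saying what is measured.

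Section 14 expects dropout: "If 20% loss of participants to follow-up is considered", "a total of 108 participants is required in each group". Section 15 describes a "simple randomisation technique with a 1:1 allocation ratio". Section 18 lists as a secondary outcome "Clinic attendance, using clinic registers".

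**The concern.** The observed-data clause is a rule that the protocol states, not a gap left for a statistical analysis plan. With one post-baseline value per participant, both named tests use only those who have that value. The estimate then describes participants who came back at six months, although the label suggests everyone randomised.

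The trial's own premises make loss related to both arm and outcome plausible. Section 1 of the objectives list asks whether SMS works as an appointment reminder, and attendance is an outcome. Only one arm receives daily messages and reminders. The introduction treats poor adherence as a main cause of poor control. If messages change who attends, they may also change who is measured, and the reasons for loss can differ between arms even when the rates are equal. What is at stake is the size, and possibly the sign, of the error in the primary comparison.

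**Working it through.** **Inputs.** From section 14: difference 0.5, SD 1, two-sided alpha 5%, 90 per arm before loss, 20% loss, 108 per arm after. These are HbA1c figures, while the primary outcome is random glucose, so the results below are best read in SD units. The protocol gives no loss rates by arm and no gap between lost and seen participants; both are assumed here and shown as ranges.

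**The plan's own figures.** With 90 per arm, a difference of 0.5 and SD 1, the normal approximation gives 91.8% power (91.6% by the t distribution), which agrees with "the two-tailed calculation gives a power of over 90% with only 90 participants in each of the control and intervention group". The stated enrolment is 90 × 1.2 = 108.

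**Who is analysed.** 108 × 0.8 = 86.4 per arm. Over both arms, 216 × 0.2 = 43.2 participants have no primary value. Power with 86.4 per arm is 90.8%.

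**Bias.** Let d be the share lost in an arm, and gap the mean outcome of those lost minus that of those seen (higher is worse). The complete-case comparison overstates the SMS benefit by

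d(SMS) × gap(SMS) − d(control) × gap(control).

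| Loss, SMS / control | Gap, SMS / control (SD) | Bias (SD) | Share of planned 0.5 |
|---|---|---|---|
| 20% / 20% | 0.5 / 0.5 or 1 / 1 | 0 | 0% |
| 20% / 20% | 0.5 / 0 | +0.10 | 20% |
| 20% / 20% | 1 / 0 | +0.20 | 40% |
| 25% / 15% | 0.5 / 0.5 to 1 / 1 | +0.05 to +0.10 | 10% to 20% |
| 30% / 10% | 0.5 / 0.5 to 1 / 1 | +0.10 to +0.20 | 20% to 40% |
| 15% / 25% | 0.5 / 0.5 to 1 / 1 | −0.05 to −0.10 | 10% to 20%, against SMS |
| 10% / 30% | 0.5 / 0.5 to 1 / 1 | −0.10 to −0.20 | 20% to 40%, against SMS |

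**Effect on the test.** With 86.4 per arm the standard error is √(2/86.4) = 0.152. Under no true effect, a bias of 0.05, 0.10 or 0.20 raises the nominal 5% type I error to about 6.2%, 10.1% or 26.0%. If the true effect is 0.5 and the same bias works against SMS, power falls to about 84%, 75% or 50%.

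**What adjustment can do.** A null simulation used 108 per arm, about 20% loss in each arm, a baseline to six-month correlation of 0.5, and loss at random in control.

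- When loss in the SMS arm depended on baseline, the bias in the six-month mean difference was 0.09 unadjusted and about 0 after baseline adjustment.
- When loss in that arm depended on the outcome itself, the bias was 0.17 unadjusted and 0.13 adjusted, with an adjusted type I error of about 18%.

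**The case against.** **Much of this is analysis-plan content.** Covariates, imputation models and sensitivity analyses are commonly left to a later plan, and naming no covariates does not exclude them. That is fair, and their absence is not the point. The point is the clause that fixes the analysis on observed data: a primary analysis that imputed missing values would depart from it. An imputed sensitivity analysis would not.

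**The analysis is valid unless the arms differ.** A reader might infer that the comparison is sound only if loss is unrelated to glucose. The formula does not support that: equal loss and equal gaps give zero bias even if those lost are much worse. The only loss figure in the protocol is a single 20%, applied to both groups.

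**The direction is unknown.** A reader might also infer that the SMS benefit will be inflated. The documents do not support this either. Reminders could improve retention in the SMS arm, and with the same gap the bias then runs against SMS.

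**The outcome is already a change from baseline.** This helps less than it seems. With equal SDs and the simulation's correlation of 0.5, a bias of −0.09 in the six-month difference from baseline-driven loss implies that those seen in the SMS arm are shifted by −0.09 / 0.5 = −0.18 at baseline. The change score then carries (0.5 − 1) × (−0.18) = +0.09, the same size with the opposite sign. For outcome-driven loss the change score roughly halves the bias: 0.5 × 0.17 ≈ 0.09.

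**Imputation is not a cure.** This stands. Imputing from baseline variables alone adds little to a baseline-adjusted complete-case regression, and does not remove outcome-driven bias. Any gain must come from an auxiliary variable such as attendance, whose predictive strength is unknown, and the remaining risk has to be shown by sensitivity analysis.

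**Conclusion.** The concern holds in a limited form. Followed as written, section 21 gives a complete-case comparison of about 86 of 108 per arm at the planned loss. It may be biased, for or against SMS, if the rate or causes of loss differ between arms. On assumed gaps of 0.5 to 1 SD, a 10-point difference in loss gives 0.05 to 0.10 SD and a 20-point difference 0.10 to 0.20 SD. Equal loss with equal gaps gives none. The gaps and the splits are assumptions, and the scale is borrowed from the HbA1c inputs of section 14.

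Two further readings should be avoided. The intention-to-treat label is not wrong about analysing people in their allocated arm; what is lost is coverage of all randomised. And the trial is not underpowered on this account, since power after the planned loss stays just above 90%. The change is worth making because the primary comparison is exposed and the remedy is cheap.

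**What to change.** Replace the observed-data clause in section 21 with the following:

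- All randomised participants are analysed in their allocated arm. The six-month glucose value is compared by linear regression on arm, adjusted for baseline glucose, clinic, age and diabetes duration.
- Missing six-month values are handled under a stated missing-at-random assumption by multiple imputation within arm, with clinic-register attendance as an auxiliary variable. The adjusted complete-case result is reported alongside.
- A delta-shift sensitivity analysis makes lost participants worse in each arm in turn, over a stated range.
- Loss and its reasons are reported by arm.

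These variables are already planned in sections 15, 16 and 18. Register attendance should be obtainable for participants who miss the study visit; the sponsor should confirm this. Adjusting for clinic presumes individual randomisation within clinics. Section 15 also speaks of separate districts for the two arms, and that must be reconciled first, as must the choice between chi-square and regression. The cost is some extra analysis work; no new data are needed.

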**17. PRIMARY OUTCOME MEASURE**

**17.1 Glycaemic control**

The primary outcome measure is a change in glycaemic control from baseline to six months, measured as mean random blood glucose level. This will be assessed using a point-of care device which analyses a drop of fingertip capillary blood.

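### Section 21 assigns both a chi-square test and a linear regression to a continuous primary outcome, gives no cut-off for the chi-square, and does not say which analysis decides

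*Protocol*

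**What the plan says.** Section 17.1 defines the outcome on a continuous scale: "The primary outcome measure is a change in glycaemic control from baseline to six months, measured as mean random blood glucose level".

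Section 14 sizes the trial on a difference in means with a standard deviation: "Standard care for diabetes using metformin has been reported to reduce HbA1c by 1% and the intervention adds an extra 0.5" percentage points, then "Assuming a standard deviation of 1 and an alpha error level of 5" per cent. It concludes that "the two-tailed calculation gives a power of over 90% with only 90 participants in each of the control and intervention group".

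Section 21 makes two statements about how that outcome is analysed. The first is "Primary outcome will be analysed with the chi-square". The second, later in the same paragraph, is "Linear regression model will be used to test the effect of intervention on the primary outcome between the two groups". The error level is common to everything: "All statistical tests will be two-sided at 5% significance level". No order, split of alpha or deciding test is given.

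The section on key operational terms describes glycaemic control as keeping glucose in the normal range, without a number. The only numerical glucose value tied to participants is the 10 mmol/l entry criterion in Section 13.1, which is an alternative to an HbA1c criterion.

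**The concern.** A chi-square test compares proportions. The stated primary outcome is a change in a mean and has no categories, so the test does not fit it as written. Running it would require a cut-off that the protocol does not contain. Three things follow.

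- A cut-off chosen late could be chosen with the data in view.
- Dichotomising a continuous measure throws away information that the sample size calculation counts on.
- With two unranked analyses of one outcome, the two may disagree, and nothing in the text says which result is the trial's answer.

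A separate SAP would not remove the problem. It could settle the matter only by overriding one of the two sentences.

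**Working it through.** **Inputs.** Difference 0.5, SD 1, two-sided alpha 5%, 90 evaluable per arm, 108 enrolled per arm and 20% loss (all Section 14); 1:1 allocation (Section 15). After loss, 108 × 0.8 = 86.4, so 86 per arm. Assumed here: a normal outcome with equal variances, individual randomisation without clustering, and a cut-off, because none is given. The effect size is an HbA1c figure, so what follows shows a 0.5 SD effect and does not predict results for random glucose.

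**1. The plan's own figure.** Power = Φ(δ / (σ√(2/n)) − 1.96).

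- n = 90: 0.5/√(2/90) = 3.354; 3.354 − 1.960 = 1.394; power 91.8% (exact t-test 91.6%).
- n = 86: 0.5/√(2/86) = 3.279; 3.279 − 1.960 = 1.319; power 90.6% (exact t-test 90.3%).

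The stated power of over 90% reproduces, but for a comparison of means.

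**2. Chi-square on a dichotomised outcome.** Let p_C be the share of controls below the cut. With a 0.5 SD shift, p_I = Φ(Φ⁻¹(p_C) + 0.5). With d = p_I − p_C and p̄ their average,

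power = Φ((d − 1.96·s₀)/s₁), where s₀ = √(2p̄(1 − p̄)/n) and s₁ = √((p_C(1 − p_C) + p_I(1 − p_I))/n).

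The best cut lies midway between the two means: p_C = 0.4013, p_I = 0.5987, d = 0.1974. At n = 86, s₀ = 0.07625 and s₁ = 0.07475, so (0.1974 − 0.1494)/0.07475 = 0.64 and power is 73.9%.

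| Controls below cut | Intervention below cut | Power, 86 per arm | Power, 90 per arm | n per arm for 90% power |
|---|---|---|---|---|
| 10% | 21.7% | 55.8% | 57.7% | 202 |
| 16% | 31.0% | 64.5% | 66.5% | 165 |
| 20% | 36.6% | 68.0% | 70.0% | 153 |
| 30% | 49.0% | 72.7% | 74.6% | 137 |
| 40.1% (best) | 59.9% | 73.9% | 75.9% | 133 |
| 50% | 69.1% | 72.9% | 74.9% | 136 |

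The comparison of means needs 85 per arm for 90% power. At 86 per arm the loss from dichotomising runs from 90.6 − 73.9 = 16.7 to 90.6 − 55.8 = 34.8 percentage points. The 16% row mirrors the 84% uncontrolled rate that the introduction cites for the province. It is only an example, since Section 13.1 admits patients selected for poor control.

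**3. Type I error if either test could count.** Two independent tests at 5% would give 1 − 0.95² = 9.75%. These two use the same data and are correlated, so the rate is lower. Simulation with no effect (50,000 trials, 90 per arm, t-test and uncorrected chi-square, one fixed cut) gave 7.5% with 50% below the cut, 8.1% with 30%, 8.4% with 16% and 8.9% with 10%. This step needs no effect size.

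**4. Disagreement.** In the same simulation with the 0.5 SD effect present, the two tests differed on significance in about 18% to 36% of trials, depending on the cut.

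**The case against.** The strongest reply is that the protocol already contains a usable analysis. Only the regression sentence speaks of testing the intervention effect between the groups; the chi-square sentence names no comparison and may be a careless line. On that reading there is one test, the error rate is 5%, and the power of the trial is unaffected. This stands in part. A reader might infer that the plan sets two primary tests and claims success on either. The documents do not say so: neither analysis is labelled the primary test and no success rule is given. The inflated error rate is therefore conditional. It is not a property of the plan as written. For the same reason the chi-square powers do not show that the trial is underpowered.

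A second reply is that the chi-square has a visible source: the outcome is called glycaemic control, which is described as being in the normal range, and 10 mmol/l appears among the entry criteria. The first part explains where the sentence may have come from, but supplies no number. A reader might infer that 10 mmol/l is the intended cut-off. The protocol uses it only as one of two alternative routes into the trial, never as a definition of control, and patients admitted on HbA1c may already be at or below it at baseline.

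What remains is that the chi-square sentence refers expressly to the primary outcome, does not fit that outcome, and is left unranked beside the regression.

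**Conclusion.** The concern holds as a contradiction within the protocol. One sentence of Section 21 assigns to the primary outcome a test that cannot be run on it as defined; another assigns a test that can; the text does not choose between them. This conclusion rests on Sections 14, 17.1 and 21 alone and needs no calculation.

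The size is illustrative. For a normal outcome and a 0.5 SD effect, making the chi-square decisive would cost about 17 to 35 points of power at 86 per arm for cuts with 10% to 50% of controls below them. Accepting either test would put the type I error at about 7% to 8% for most single fixed cuts, and near 9% for the most extreme cut examined. A cut chosen after seeing the data would add further freedom. Because the Section 14 effect and SD are for HbA1c, the absolute powers do not carry over to random blood glucose.

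**What to change.** In Section 21, delete "Primary outcome will be analysed with the chi-square". Replace the regression sentence with one that names a single primary analysis at two-sided 5%: linear regression of six-month random blood glucose on arm, adjusted for baseline random blood glucose. The baseline adjustment matters because Section 17.1 defines a change from baseline. With it, the arm coefficient is the same as in a baseline-adjusted regression of the change, so the analysis estimates the between-arm difference in change and leaves the outcome as defined.

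If a proportion controlled is wanted, list it as secondary in Section 18, with a threshold that the investigators fix and justify before any outcome data are seen.

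The cost is two edited sentences in Section 21 and, if the secondary analysis is kept, one line in Section 18. Baseline random blood glucose is already collected (Section 16), so recruitment, visits and sample size do not change. The edit does not settle which glycaemic measure is meant: Section 15 describes the primary outcome as both random and fasting, and Section 21 also compares HbA1c readings. Those references should be reconciled in the same revision.

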**22. CHAPTER OUTLINES**

Chapter one of the study will orientate the reader about the study. Chapter two will focus on relevant literature pertaining broadly, to the use of mHealth technology and diabetes control. Chapter three will include the research methodology. Chapter four will focus on the results, represented in tables, graphs and charts as well as the discussion of findings. Summary, conclusion and recommendations will be presented in chapter five.

**23. RESULTS DISSEMINATION**

The thesis will be kept in the school’s library. Likewise, results will be presented at seminars and conferences. Lastly, the findings of this study will be published in accredited peer reviewed journals.

**24. TIME FRAME**

The proposed timeline for the study is illustrated in Table 1.

**Table 1**: Timeline for the research project

|  | Months | | | | | | | | | | | | | | | | | |  |
| --- | --- | --- | --- | --- | --- | --- | --- | --- | --- | --- | --- | --- | --- | --- | --- | --- | --- | --- | --- |
| Activity | April 2017 | May, 2017 | June, 2017 | July, 2017 | Aug 2017 | Sept 2017 | Oct. 2017 | Nov. 2017 | Dec. 2017 | Jan, 2018 | Feb, 2018 | Mar, 2018 | April 2018 | May 2018 | June, 2018 | July 2018 | Aug., 2018 | Sept..2018 | May 2019 |
| Writing of research proposal |  |  |  |  |  |  |  |  |  |  |  |  |  |  |  |  |  |  |  |
| Literature review |  |  |  |  |  |  |  |  |  |  |  |  |  |  |  |  |  |  |  |
| Presentation of proposal to the faculty |  |  |  |  |  |  |  |  |  |  |  |  |  |  |  |  |  |  |  |
| Registration with senate higher degree committee |  |  |  |  |  |  |  |  |  |  |  |  |  |  |  |  |  |  |  |
| Registration with the provincial Department of Health |  |  |  |  |  |  |  |  |  |  |  |  |  |  |  |  |  |  |  |
| Registration with the Districts Department of Health |  |  |  |  |  |  |  |  |  |  |  |  |  |  |  |  |  |  |  |
| Formulation of the SMS by the team |  |  |  |  |  |  |  |  |  |  |  |  |  |  |  |  |  |  |  |
| Training of research assistant |  |  |  |  |  |  |  |  |  |  |  |  |  |  |  |  |  |  |  |
| Baseline Data collection |  |  |  |  |  |  |  |  |  |  |  |  |  |  |  |  |  |  |  |
| Data capturing |  |  |  |  |  |  |  |  |  |  |  |  |  |  |  |  |  |  |  |
| Collection of data after 3 months |  |  |  |  |  |  |  |  |  |  |  |  |  |  |  |  |  |  |  |
| Literature review continues |  |  |  |  |  |  |  |  |  |  |  |  |  |  |  |  |  |  |  |
| Collection of data after 6 months |  |  |  |  |  |  |  |  |  |  |  |  |  |  |  |  |  |  |  |
| Data capturing |  |  |  |  |  |  |  |  |  |  |  |  |  |  |  |  |  |  |  |
| Data Analysis |  |  |  |  |  |  |  |  |  |  |  |  |  |  |  |  |  |  |  |
| Compilation of reports |  |  |  |  |  |  |  |  |  |  |  |  |  |  |  |  |  |  |  |
| Submission for examination |  |  |  |  |  |  |  |  |  |  |  |  |  |  |  |  |  |  |  |
| Final corrections |  |  |  |  |  |  |  |  |  |  |  |  |  |  |  |  |  |  |  |
| Graduation |  |  |  |  |  |  |  |  |  |  |  |  |  |  |  |  |  |  |  |

